#### Pregnancy complications, other diseases or symptoms and maternal outcomes

Gestational hypertension: Blood pressure and will be measured twice by obstetricians to the nearest 2 mmHg with the desktop mercury sphygmomanometer (Yuwell, Danyang, Jiangsu, China). Two measurements will be taken after 2-min intervals. Hypertension of pregnancy will be defined as systolic blood pressure of > 140/90 mmHg and/or diastolic blood pressure of ≥90 mmHg sustained on two measurements.

Gestational diabetes mellitus (GDM): Blood glucose will be determined with elbow venous blood using an osmotic pressure molar concentration meter (SMC 30C; Tianhe, Tianjin, China) by laboratory physicians. GDM will be diagnosed based on the results of the 100-g, 3-h oral glucose tolerance test (OGTT) by obstetricians. According to the recommendations of the Committee on Obstetric Practice, a definite diagnosis is made if two or more thresholds be met or exceeded. The threshold of fasting blood glucose is as follows:5.3 mmol/L, 10.0 mmol/L for blood glucose of 1 h, 8.6 mmol/L for blood glucose of 2 h and 7.8 for blood glucose of 3 h [62].

Preeclampsia or eclampsia: Urine protein will be assessed using an automatic biochemical analyzer (Cobas C501; Roche; Basel, Switzerland) by laboratory physicians. Preeclampsia will be diagnosed at ≥20 weeks’ gestation along with new-onset gestational hypertension and new-onset proteinuria [63]. Eclampsia will be defined as the development of convulsions and/or unexplained coma during or after pregnancy with symptoms of preeclampsia, which will be diagnosed by obstetricians [64].

Anemia: Hemoglobin of elbow venous blood will be tested using automatic routine blood test device (MC-600, Kubeier, Shenzhen, China) by laboratory physicians. Anemia will be defined as < hemoglobin 110 g/L.

Oligohydramnios: Amniotic fluid will be measured using ultrasonography by professional medical technicians. Oligohydramnios is diagnosed by an amniotic fluid index (AFI) of < 5 cm or maximum amniotic fluid pool depth of < 2 cm [65].

Urinary tract infection: The diagnostic criteria is based on symptoms or laboratory confirmation including white blood cells and bacteria in urine by obstetricians. Routine urine test will be conducted using an automatic biochemical analyzer (Cobas C501; Roche; Basel, Switzerland) by laboratory obstetrician.

Spontaneous abortion: It will be recorded by obstetricians.

Preterm labor: It is defined as giving birth between 28 weeks’ and less than 37 weeks’ gestation. It will be diagnosed by obstetricians.

Mode of delivery: There are two modes: namely natural childbirth and cesarean section, which will be recorded by obstetricians.

Breast milk: The time for early initiation of breastfeeding will be recorded [66]. And the amount of breast milk will be evaluated based on the performances of infant after breast feeding.

Functional constipation: According to the Rome III criteria, it will be defined when participants present at least two of the following symptoms: at least one quarter of defecations for the last 12 weeks: lumpy or hard stools; straining; sensation of incomplete evacuation; sensation of anorectal obstruction; manual maneuvers to facilitate defecation; fewer than three defecations per week. Loose stools are rarely present without the use of laxatives [67]. Functional constipation will be diagnosed by obstetricians.

Total gestational weight gain (GWG) and postpartum weight retention (PWR): Both of them will be calculated based on weight of participants. GWG (kg) = weight before pregnancy (kg) -weight before delivery (kg). GWG will be assessed according to the recommendation of Institute of Medicine (IOM) [68]. PWR (kg) = weight before pregnancy (kg) - weight at 42 days after childbirth (kg).

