#### Indicators related to hydration state

About the evaluation criteria and indicators for hydration state, multiple indicators will be used for comprehensive evaluation, so body fluids, fluid intake, urine and blood osmolality are measured for evaluating hydration state in this study. At present, the internationally recognized and authoritative indicator is urine osmolality, which will be used as the primary determinant of the hydration state in this analysis of this study, and other indicators will be considered to be auxiliary indicators.

Intracellular fluid (ICF) and extracellular fluid (ECF): It will be measured by professional obstetricians using a body composition analyzer (Inbody 720; Inbody; Seoul, Korea) with the patients in a fasting state and after having defecated and urinated [59–61].

Urine and blood osmolality: The first morning urine samples will be collected in a sterile disposable urine sample cup, and blood will also be collected in vacuum tubes. Using an osmotic pressure molar concentration meter (SMC 30C; Tianhe, Tianjin, China) with the freezing-point method, osmolality will be determined by laboratory physicians, which will be used to assess the hydration state of participants.

Urine-specific gravity (USG): Using an automatic urinary sediment analyzer (FUS-200, Dirui, Changchun, China) with the uric dry-chemistry method, the first morning urine samples will be collected in sterile disposable urine sample cup to determine USG by laboratory physicians.

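### Two outcome definitions are wrong as written: the systolic limit for hypertension of pregnancy is a pressure pair with no onset condition, and blood glucose for GDM is assigned to an osmometer

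*Protocol article*

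**What the plan says.** All the definitions at issue are in the protocol article, *Pregnancy complications, other diseases or symptoms and maternal outcomes*, unless another section is named.

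- **Hypertension of pregnancy** is "systolic blood pressure of > 140/90 mmHg and/or diastolic blood pressure of ≥90 mmHg sustained on two measurements". Pressure is read "to the nearest 2 mmHg with the desktop mercury sphygmomanometer". The only repeat described is: "Two measurements will be taken after 2-min intervals". No gestational age and no new-onset requirement is attached.
- **Preeclampsia** is built on that diagnosis but has its own timing: "Preeclampsia will be diagnosed at ≥20 weeks’ gestation along with new-onset gestational hypertension", together with new proteinuria.
- **GDM** is diagnosed by obstetricians from a 100-g, 3-hour glucose tolerance test when at least two of four thresholds are reached: 5.3, 10.0 and 8.6 mmol/L, and 7.8 with no unit printed. On measurement it says: "Blood glucose will be determined with elbow venous blood using an osmotic pressure molar concentration meter (SMC 30C; Tianhe, Tianjin, China) by laboratory physicians".
- **Osmolality**, in *Indicators related to hydration state*, is measured with the same model: "Using an osmotic pressure molar concentration meter (SMC 30C; Tianhe, Tianjin, China) with the freezing-point method, osmolality will be determined by laboratory physicians".

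Table 3 and *Study procedure* have pregnancy complications assessed at 15–17, 20–22 and 30–32 weeks and around childbirth.

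**The concern.** The second study hypothesis and the third objective are about associations between hydration and pregnancy complications. The case definitions set the dependent variable of the planned logistic models, so a faulty definition passes straight into the results.

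For hypertension, two centres, or two obstetricians in one centre, could read the printed rule differently and count different women. For GDM, a laboratory that followed the text would run the tolerance-test samples on an instrument that reports the total of dissolved particles, not glucose. No analysis plan written later can recover a concentration that was never assayed. These are also details the article chose to state, so they are not omissions caused by condensing a longer protocol.

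**Working it through.** No stated figure has to be reproduced here. The check sets the wording side by side and follows the logic.

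**1. The systolic limit.** The printed rule joins a systolic part and a diastolic part with and/or. The systolic part can be read in two ways.

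- *Reading A: the second number is a slip.* A case has systolic above 140, or diastolic at least 90.
- *Reading B: the pair is literal.* A case has systolic above 140 with diastolic above 90, or diastolic at least 90. The first branch lies wholly inside the second, so the rule reduces to diastolic at least 90 and systolic pressure plays no part.

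**2. The inequality.** Readings are recorded in 2-mmHg steps, so the first recorded systolic value above 140 is 140 + 2 = 142, and the last diastolic value below 90 is 90 − 2 = 88.

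| Sustained reading | Reading A, strict as printed | Reading A, if inclusive | Reading B |
|---|---|---|---|
| 140/88 | not a case | case | not a case |
| 142/88 | case | case | not a case |
| any systolic with diastolic 90 | case | case | case |

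Only women with diastolic below 90 are affected. Within reading A, the choice between strict and inclusive matters only when a systolic reading of exactly 140 decides the case.

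**3. How many readings could fall on 140.** The document gives no blood-pressure distribution, so this is an illustration under assumed normal distributions. A recorded 140 covers true values from 139 to 141.

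| Assumed mean/SD (mmHg) | P(recorded ≥140) | P(recorded ≥142) | Difference = P(recorded 140) | Share of readings ≥140 |
|---|---|---|---|---|
| 115/12 | 0.0228 | 0.0151 | 0.0076 | 33% |
| 120/12 | 0.0567 | 0.0401 | 0.0166 | 29% |
| 125/14 | 0.1587 | 0.1265 | 0.0321 | 20% |

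Multiplied by 380, the difference is about 3, 6 and 12 women for one single reading. This ignores the second reading, the repeated visits and the diastolic route to a diagnosis. It shows that the inequality is not a formality, but it does not estimate misclassified cases.

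**4. Onset.** Complications are assessed at 15–17 weeks, and hypertension of pregnancy has no lower limit of gestational age. A raised pair of readings at that visit therefore meets the definition as written. Preeclampsia, in the same section, cannot be diagnosed before 20 weeks and requires the hypertension to be new. Whether hypertension first seen before 20 weeks counts as new-onset gestational hypertension for that purpose is left open.

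**5. The glucose instrument.** Model, maker and place are identical in the GDM text and the osmolality text. The osmolality text gives the principle as freezing point, which responds to all dissolved particles together. The GDM rule needs four glucose concentrations. An osmolality reading does not supply them, and the article names no other instrument for glucose. A biochemical analyser (Cobas C501) is named in the same section, but for urine protein and routine urine testing.

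**The case against.** The strongest reply is that these are slips of wording in a study that calls itself preliminary and exploratory, and that obstetricians will make the diagnoses. Much of this is fair, and it rules out several stronger readings.

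- **A reader might infer that GDM cannot be diagnosed at all.** The document does not support that. The decision rule (test, four thresholds, at least two reached) is complete apart from one unit. The instrument is probably copied from the osmolality text. What stands is that the stated measurement method is wrong.
- **A reader might infer that the 2-minute repeat makes the hypertension rule unusable or inadequate.** It can be carried out as written, and the *Discussion* gives accuracy as the reason for measuring pressure twice. Calling it too weak for a sustained rise needs a standard that the document does not contain.
- **A reader might infer that pre-existing hypertension will be counted as an outcome.** *Participants* excludes cardiovascular and other diseases, and *Study procedure* collects disease history at entry and records when each outcome occurs. This reduces the problem and makes early onset identifiable. It does not supply the missing onset condition.
- **A reader might infer that preeclampsia inherits every fault.** It has its own 20-week and new-onset conditions, so it inherits the systolic limit but largely not the timing gap.
- **A reader might infer a bias from one device measuring both exposure and outcome.** Nothing in the document supports this.
- **A reader might treat these as the trial's headline outcomes.** The article ranks no complication. The sample size rests on new-onset hyperglycemia, and its calculation is not affected by this point.

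The difference between a strict and an inclusive limit is not a contradiction in itself. It needs attention because it sits inside a limit that is already malformed.

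**Conclusion.** The point holds for two definitions. The limit for hypertension of pregnancy is malformed: it is a pair of pressures for one quantity, with an inequality that differs from the diastolic one without explanation. On its two literal readings, women with systolic above 140 and diastolic below 90 are either all cases or none. The same definition lacks an onset condition that its neighbour, preeclampsia, has, although assessment begins at 15–17 weeks. Blood glucose is assigned to an instrument that the protocol itself describes as measuring osmolality.

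The textual conclusions need no outside figure. That a freezing-point reading does not isolate glucose follows from the stated method. The only assumed numbers are the blood-pressure distributions in the illustration, under which 20% to 33% of single systolic readings at or above 140 would be recorded as exactly 140. The true effect on the case count, and on any association, cannot be derived from the document. The correction is cheap and should be made before outcomes are classified.

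**What to change.** In the section on pregnancy complications:

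1. Reconcile the blood-pressure wording so that it gives one systolic and one diastolic limit, each with an inequality chosen on purpose.
2. Reconcile the onset condition of gestational hypertension with the preeclampsia definition and with the 15–17-week visit, and say how hypertension first seen before 20 weeks is classified. The occurrence times already being recorded are enough to apply the rule.
3. Replace the osmometer in the GDM text with the glucose assay actually used, for example on the biochemical analyser already named there if that is what the laboratory runs.
4. Print the unit on the 3-hour glucose threshold.

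The authors decide the clinical cut-offs and any rule for confirming a raised pressure; this review proposes none. The cost is protocol wording only, with possibly a small change in the number of women counted as hypertensive.

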The most considerable challenges in this study is the following up of participants and quality control. Important protocol modifications will be discussed and determined by the researcher group, and will be communicated to investigators, trial participants and other relevant parties by e-mail immediately. In the study, participants will be followed up from the first trimester of pregnancy to 42 days after childbirth. To increase the rate of follow up, effective and convenient methods of communication between participants and researchers will be established, including telephone call, home visits, e-mail, WeChat, short message and so on. The content and purpose of the study will be clearly clarified to establish a relationship of trust and raise awareness of participants concerning the importance of the study. In this study, many methods will also be used to ensure the quality control. The requirements for participants will be fully explained. Participants will also be trained to be familiarized with the content of related questionnaires and study requirements. If a participant failed to follow the requirements, her data will not be included in this study and the reason for dropout will also be recorded. Researchers will be trained on the procedure of this trial, the content of the questionnaires and the technology-related laboratory tests. Some indicators such as height, weight, and blood pressure will be measured twice for accuracy, such as height, weight and blood pressure. Food models and photographic models will be provided to help participants fill the questionnaire related to food and fluid intake after training to enhance estimation accuracy. Physiological indexes, such as blood and urine indicators, will be tested immediately after collection, in order to ensure the accuracy, and will be tested by laboratory physicians with the minimum 5 years of clinical experience to ensure accuracy. Trial conduction will be audited by a competent authority in the hospital every day, and the process will be independent from investigators and the sponsor. All the questionnaires will be regularly checked and stored for researcher rechecks. A data monitoring committee (DMC) is established and is comprised by six members (three clinicians, one statistician, one ethicist and one nutritionists), who are independent of the sponsor and competing interests. DMC will review the procedure and data of the study for once a week. The six members will evaluate the safety concerns and benefits to decide that if the study should be continued or terminated. They will also examine the quality of the data, supervise the quality control, record the follow-up process and supervise the process of data entry and analysis. Four hydration and fluid intake related projects has been completed in China by our team; these provided an authoritative questionnaire and technical supports for the study.

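### The gestational hypertension rule gives a pressure pair with a strict sign as its systolic limit and calls readings 2 minutes apart sustained, so hypertension and preeclampsia can be misclassified

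*Protocol article*

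**What the plan says.** All of this is in the protocol article. Under Pregnancy complications, other diseases or symptoms and maternal outcomes, the Gestational hypertension entry says that blood pressure is "measured twice by obstetricians to the nearest 2 mmHg with the desktop mercury sphygmomanometer". It continues: "Two measurements will be taken after 2-min intervals". A case is then "systolic blood pressure of > 140/90 mmHg and/or diastolic blood pressure of ≥90 mmHg sustained on two measurements".

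The Preeclampsia entry in the same section builds on this: "Preeclampsia will be diagnosed at ≥20 weeks’ gestation along with new-onset gestational hypertension and new-onset proteinuria". Eclampsia in turn requires symptoms of preeclampsia.

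The Discussion, on quality control, gives the purpose of repeating the measurement: "Some indicators such as height, weight, and blood pressure will be measured twice for accuracy".

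Pregnancy complications are among the outcomes listed in Table 1. No other section gives a single-valued systolic limit, a second occasion or a longer interval between readings.

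**The concern.** Three features of the rule do not fit together.

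- **Pair as a limit.** One pressure cannot exceed a pair, so the systolic limb cannot be applied literally.
- **Mixed signs.** The systolic sign excludes its limit and the diastolic sign includes it. On a scale read in 2 mmHg steps, both 140 and 90 are recordable, so the sign decides real cases.
- **Sustained.** The word suggests that the elevation persists. Two readings 2 minutes apart belong to one sitting, and the protocol gives their purpose as accuracy.

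At stake is the case list for hypertension, for preeclampsia and, through preeclampsia, for eclampsia. These are to be compared across hydration states. If the rule can be applied in more than one way, the count cannot be reproduced. Non-differential misclassification of a binary outcome generally weakens an association.

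**Working it through.** The plan states no figure to reproduce here. The check has a textual part and an illustration under assumed values.

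**1. What the systolic limb can mean.** Suppose the pair required systolic above 140 and diastolic above 90 together. Every such woman would already meet the diastolic limb (90 or more), so the systolic limb would add no cases and the and/or would do nothing. The only reading that gives the limb a function is systolic above 140 alone. The pair is therefore probably a drafting slip, and the sign at 140 is what remains open.

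**2. How often the sign decides.** Inputs from the protocol: 2 mmHg resolution and 380 women. Assumed: systolic pressure is normal with mean *m* of 110 to 120 and SD *s* of 10 to 14 mmHg. With rounding to the nearest 2 mmHg, a recorded 140 covers 139 to 141, so:

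- P(recorded ≥ 140) = P(X > 139)
- P(recorded > 140) = P(X > 141)
- share at exactly 140 = 1 − P(X > 141) / P(X > 139)

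Example, *m* = 115 and *s* = 12: (139 − 115)/12 = 2.00 gives 0.0228, and (141 − 115)/12 = 2.17 gives 0.0151. The share is 33.5%. Among 380 women this is 8.6 against 5.7, a difference of 2.9.

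| Mean | SD | P(≥140) | P(>140) | Share at 140 | Women of 380, ≥ vs > | Difference |
|---|---|---|---|---|---|---|
| 110 | 10 | 0.0019 | 0.0010 | 48.1% | 0.7 vs 0.4 | 0.3 |
| 110 | 12 | 0.0078 | 0.0049 | 37.5% | 3.0 vs 1.9 | 1.1 |
| 110 | 14 | 0.0192 | 0.0134 | 30.0% | 7.3 vs 5.1 | 2.2 |
| 115 | 10 | 0.0082 | 0.0047 | 43.1% | 3.1 vs 1.8 | 1.3 |
| 115 | 12 | 0.0228 | 0.0151 | 33.5% | 8.6 vs 5.7 | 2.9 |
| 115 | 14 | 0.0432 | 0.0316 | 26.8% | 16.4 vs 12.0 | 4.4 |
| 120 | 10 | 0.0287 | 0.0179 | 37.8% | 10.9 vs 6.8 | 4.1 |
| 120 | 12 | 0.0567 | 0.0401 | 29.3% | 21.5 vs 15.2 | 6.3 |
| 120 | 14 | 0.0874 | 0.0668 | 23.5% | 33.2 vs 25.4 | 7.8 |

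Shares were computed before rounding. They refer to one systolic reading and leave out the diastolic limb.

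**3. Adding the diastolic limb.** A woman at 140 systolic with diastolic 90 or more is a case under either sign. A simulation of the whole rule used three visits with two readings each. It assumed a diastolic mean of 70 to 75, a systolic–diastolic correlation of 0.6 to 0.7, and diastolic SDs 0.75 times the systolic ones. Changing the sign altered the case count by roughly 1% to a third. The width of that range shows how strongly it depends on the assumptions.

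**4. Sustained against duplicate.** Readings in one sitting share that sitting's pressure level. Repeating them reduces reading error but says little about whether the level persists. As an illustration, assume a mean of 115 to 120, between-woman SD 10, between-occasion SD 5 to 8 and reading error SD 3 to 4. Requiring both same-sitting readings to be 140 or more then flags 1.5 to 2.8 times as many women as requiring it on two occasions. This shows only that the two are different criteria. The model holds each woman's usual pressure constant and contains no disease onset.

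**The case against.** The strongest reply is that this is a wording slip in one of many outcomes of a self-described preliminary exploratory study, whose sample size rests on hyperglycemia. Pressures are read to 2 mmHg, so if the readings are kept, any limit can be reapplied at analysis. The Study procedure section also has the onset time, duration and treatment of complications recorded, which partly addresses persistence. All of this stands, and it limits the severity. It does not repair the rule, which the article itself fixes.

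A reader might infer more than the documents support:

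- **That isolated systolic hypertension is lost** because both pressures must be raised. That reading makes the systolic limb redundant, so it is an unlikely intention.
- **That a quarter to a half of cases are lost.** The 24% to 48% is a share of single systolic readings in a rare tail, not of women meeting the whole rule.
- **That women flagged at only one visit had transient elevations.** A woman whose hypertension begins by 30–32 weeks would also be flagged at only one antenatal visit, and a model without onset cannot separate the two.
- **That a case must be confirmed on a separate occasion.** The protocol sets no minimum interval. Such a rule is a diagnostic choice that could drop late-onset cases and would cost more than a few of them.
- **That the association is biased in a known direction.** The strict sign lowers the count, while same-sitting repeats raise it relative to a persistence rule. No net effect is shown.

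**Conclusion.** The definition is wrong as written. The systolic limb has no usable single limit, its sign disagrees with the diastolic limb at a recordable value, and *sustained* is not what two readings 2 minutes apart, repeated for accuracy, can show. Hypertension can therefore be misclassified, as can preeclampsia, which is diagnosed "along with new-onset gestational hypertension and new-onset proteinuria". The documents do not show that women are in fact misclassified, or how many.

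On single systolic readings the sign affects about 0.3 to 8 of 380 women under the assumed means and SDs, and the effect on the whole rule is smaller. All blood pressure parameters are assumptions. The textual conflict does not depend on them. This is a minor to moderate correction and does not threaten the study as a whole.

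**What to change.** For the study endpoint only, leaving care unchanged:

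1. State one systolic and one diastolic limit, each as a single value in mmHg, with consistent inequality signs, joined by and/or.
2. Record both readings and apply that rule to them at analysis, so that every case is classified in the same way. Preeclampsia then uses the same rule.
3. Reconcile *sustained* with the 2-minute duplicate readings by saying what the two readings establish. If persistence is not shown, report single-sitting elevations as such.

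The choice of limits, and of any confirmation interval, is the sponsor's. The cost is protocol wording and a data-entry rule. The case count may change slightly.

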Few studies have explored the associations of fluid intake and hydration state with pregnancy complications and maternal/infant outcomes. A prospective study in Italy involving 173 pregnant women revealed that total body water and intracellular and extracellular fluid in healthy pregnant women increased gradually throughout pregnancy, but an opposite trend was observed among women with gestational hypertension [25]. In a study conducted in Canada, the body compositions of 196 women 4 and 12 h postpartum were measured: the total body water of women without arterial hypertension was 44 L, whereas that of women with arterial hypertension was only 18 L [26]. This suggested that associations might exist between water retention and the development of hypertension. A US study showed that total body water may be a strong predictor of pre-eclampsia [27]. A Mexican study suggested that total body water in pregnant women with gestational hypertension and severed eclampsia was relatively higher than that in healthy pregnant women. In addition, chronic hypovolemia induced by insufficient water intake may be among the main risk factors in the development of diabetes [28], and higher intake of boiled water may reduce the risk of diabetes [29]. Data from the US Health and Nutrition Survey (2009–2012) showed that people without optimal hydration have a greater risk of obesity than those with optimal hydration [30], suggesting that hydration influences total gestational weight gain and postpartum weight retention. One study showed that the secretion of breast milk in lactating women increased with the amount of water intake [31]. A case–control study in the United States suggested that insufficient fluid intake was a risk factor for abortion requirements and preterm births, as well as low birth weight [32]. Other studies have shown that total body water has significant effects on birth weight [26, 33–36]. A US case-control study suggested that insufficient fluid intake was an independent risk factor of low birth weight [32]. In a randomized controlled trial in California, among 40 women with normal amniotic fluid index at 28 weeks of gestation, the amniotic fluid index increased by approximately 16% in the water intervention group and approximately 8% in the control group [37]. The relationship between the state of hydration during pregnancy and the physical infant outcomes has not been fully valued and studied, so there are not so many related literatures. More studies are needed to be carried out to explore the associations between water intake, hydration state and on pregnancy complications, maternal-infant outcomes.

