During childbirth and after childbirth: Before childbirth (One day before the expected date of delivery or one day before cesarean section), psychological state, sleep quality and time, physical activities and medication-use will be collected using corresponding questionnaires. On the day of childbirth, the mode of delivery will be recorded, pregnancy complications and other complications during childbirth will be assessed and diagnosed by professional obstetricians. Infant birth weight will be measured and health state will be assessed. Breastfeeding time and the crying behavior of infants before and after breast-feeding will be recorded. At 42 days after childbirth, maternal weight retention will be measured and calculated. Secretion of breast milk and mode of infant feeding will be consulted and infant growth will be assessed. Flow-process diagram of the study was shown in Fig. 2.

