### Data entry and statistical analysis

*Data entry*: All data will be documented twice by two trained researchers using the software of Epi Data 3.1 to ensure the accuracy of data.

*Statistical analysis*: SAS 9.2 (SAS Institute Inc., Cary, NC, USA) will be used. A mixed model of repeated-measures (ANOVA) will be used to analyze the differences of outcomes among participants with different hydration state. Multi-logistic regression analysis will be used to investigate the influencing factors related to maternal health and infant outcomes, such as fluid intake, hydration state, urine osmolality, concentration of copeptin and other indicators. The level of significance will be set at 0.05 (*p* < 0.05, 2-tailed) with 95% confidence intervals (95% CI).

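### Gestational weight gain and postpartum weight retention are both defined as earlier weight minus later weight, so a gain scores negative and the direction of every effect on these outcomes is reversed

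*Protocol article*

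**What the plan says.** The definitions stand in the Methods/design part of the protocol article, in the section on pregnancy complications, other diseases or symptoms and maternal outcomes. The entry introduces the two variables by name: "Total gestational weight gain (GWG) and postpartum weight retention (PWR): Both of them will be calculated based on weight of participants". It then fixes their derivation:

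- Gain: "GWG (kg) = weight before pregnancy (kg) -weight before delivery (kg".
- Retention: "PWR (kg) = weight before pregnancy (kg) - weight at 42 days after childbirth (kg".

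Between the two formulas it adds a grading step: "GWG will be assessed according to the recommendation of Institute of Medicine (IOM".

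The variables are meant to be used. The Study procedure section schedules the second one: "At 42 days after childbirth, maternal weight retention will be measured and calculated". The Background gives the reason for studying both, citing survey data on hydration and obesity as "suggesting that hydration influences total gestational weight gain and postpartum weight retention". The statistical analysis section plans a repeated-measures mixed model that "will be used to analyze the differences of outcomes among participants with different hydration state", with two-tailed testing.

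**The concern.** A gain is the later weight minus the earlier one. Retention is what remains at day 42 above the pre-pregnancy weight. The article subtracts the later weight from the earlier one in both cases, so each formula contradicts the name of the variable it defines.

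The study asks whether dehydration goes with worse maternal outcomes, so the direction of an effect is the result of interest. With the sign reversed, a finding that dehydrated women retain more weight would be tabulated as their retaining less. The grading step is exposed in a different way: it compares a number that is negative for nearly everyone with a recommendation about kilograms gained.

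**Working it through.** There is no stated figure to reproduce; the check is on the formulas themselves.

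**Inputs.** The two formulas and the grading step come from the article. The weights below are illustrative assumptions. The Institute of Medicine ranges are not in the article; the only assumption made about them is that the lower limit L is greater than 0 kg.

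**Step 1: formulas on example weights (kg).**

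| Before pregnancy | Before delivery | Day 42 | Gain as written | Gain, later minus earlier | Retention as written | Retention, later minus earlier |
|---|---|---|---|---|---|---|
| 55.0 | 67.5 | 59.0 | 55.0 - 67.5 = -12.5 | +12.5 | 55.0 - 59.0 = -4.0 | +4.0 |
| 50 | 58 | 50 | 50 - 58 = -8 | +8 | 50 - 50 = 0 | 0 |
| 60 | 59 | 57 | 60 - 59 = +1 | -1 | 60 - 57 = +3 | -3 |

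The third woman, who lost weight, is the only one with a positive gain. The first, who gained most, has the lowest score.

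**Step 2: continuous analysis.** Let Y be the true gain (or retention). The formula as written gives -Y. For any covariate x, cov(x, -Y) = -cov(x, Y), and the residual variance is unchanged. The slope and t statistic therefore change sign, while the standard error and two-sided p-value stay the same. A mean difference between hydration groups behaves in the same way.

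A simulated data set of 342 women (380 less 10% dropout) confirms this. It assumed urine osmolality with mean 700 and SD 200 mOsm/kg, a mean gain of 12 kg, a true slope of 0.003 kg per mOsm/kg and a residual SD of 4 kg.

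| Outcome definition | Slope | t | Two-sided p | Share with negative value |
|---|---|---|---|---|
| As written | -0.0039 | -3.24 | 0.0013 | 99.7% |
| Later minus earlier | +0.0039 | +3.24 | 0.0013 | 0.3% |

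**Step 3: graded gain.** A woman with true gain g > 0 gets the value -g. Since -g < 0 < L, she falls below the recommended range whatever g is. All women who gain weight are therefore graded as gaining too little, and only a woman who lost at least L kg could be graded otherwise. In the simulated set at least 99.7% would share one grade. That leaves almost no variation to relate to hydration, and reading a coefficient backwards does not repair it.

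**Step 4: is it corrected elsewhere?** The article has no absolute value, no statement of a reversed sign convention and no second formula for either variable.

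**The case against.** The strongest reply is that this is a writing slip that reveals itself. The names and the reference to a published recommendation make the intended direction plain, and a table showing nearly all pregnant women with negative gain would be noticed at once. The article has other slips of wording, and nothing shows that the analysis would carry this one forward. For the continuous outcomes no information is lost: multiplying by -1 restores the result, and significance, precision and effect size are untouched.

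It can also be said that these outcomes have modest standing. The registered outcomes in Table 1 name maternal and infant outcomes only in general. Table 3 has one maternal weight row, apparently for retention. The sample size rests on new-onset hyperglycemia, and the study calls itself preliminary and exploratory.

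Most of this stands as a limit on the harm. It does not make the formulas right. Both are reversed in the same way, so this is not a single misplaced character. They are stated derivation rules in the Methods, not loose wording in the background. An analyst would have to depart silently from the published definition, and a reader of the results could not tell which sign was used. Recovery by a change of sign also fails for the graded version of gain if the grading is done on the values as defined.

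**Conclusion.** Both formulas are wrong as written. For every woman they return the negative of the quantity named: -12.5 kg instead of +12.5 kg for gain and -4.0 kg instead of +4.0 kg for retention in the example. If followed, they reverse the direction of every mean difference and slope for the two continuous outcomes and leave effect sizes and two-sided p-values unchanged. Assuming only that the recommended gains are positive, they also put every woman who gains weight below the recommended range.

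The damage is limited to these two outcomes. The sample size and the other pregnancy complications and infant outcomes are not affected. Whether the error has reached any analysis program cannot be told from the article.

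**What to change.** Swap the terms in both formulas:

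- Gestational weight gain (kg) = weight before delivery - weight before pregnancy.
- Postpartum weight retention (kg) = weight at 42 days after childbirth - weight before pregnancy.

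State next to them that positive values mean weight gained or retained. Make sure that whatever derivation code and variable definitions exist use the same order, and that gain is graded on the corrected value.

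The cost is two lines of text and a check of the derivation. The swap uses the same three weights that the formulas already require. The Study procedure section does not list weight among the items collected just before delivery, so it is worth confirming at the same time where that value comes from.
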